**Table 4: Grading a) for swelling**

| Grade | Diameter [mm] |
|-------|---------------|
| 0     | 0             |
| 1     | < 20          |
| 2     | 20 – 50       |
| 3     | > 50          |

**b) for redness**

| Grade | Diameter [mm] |
|-------|---------------|
| 0     | 0             |
| 1     | < 50          |
| 2     | 50 – 100      |
| 3     | > 100         |

Study subjects will be asked to indicate the maximum degree of pain they experience at the injection site using a scale ranging from 0 to 3 as described in Table 5.

**Table 5: Pain scale**

| Grade    | Description                                                                                                          |
|----------|----------------------------------------------------------------------------------------------------------------------|
| 0 | No pain at all                                                                                                       |
| 1 | Painful on touch, no restriction in movement of arms, able to work, drive, carry heavy objects as normal             |
| 2 | Painful when limb is moved
( i.e. restriction in range of movement in arm, difficulty in carrying objects) |
| 3 | Severe pain at rest
( i.e. unable to use arm due to pain.)                                                 |

All local reactions will be considered causally related to the vaccination in the absence of another more likely explanation (such as recent trauma).

At each visit subjects will be requested to report local and general side effects they might have experienced since they last were seen. The investigator will assess the severity of the solicited signs and symptoms using the key provided in Table 6.

**Table 6: Intensity of the general adverse events will be assessed as described:**

|         |                                                                                           |
|---------|-------------------------------------------------------------------------------------------|
| GRADE 0 | None                                                                                      |
| GRADE 1 | Mild: Transient or mild discomfort (< 48 hours); no medical intervention/therapy required |
| GRADE 2 | Moderate: Mild to moderate limitation in activity - some assistance may be                |

|         |                                                                                                                                          |
|---------|------------------------------------------------------------------------------------------------------------------------------------------|
|         | needed; no or minimal medical intervention/therapy required                                                                              |
| GRADE 3 | Severe: Marked limitation in activity, some assistance usually required; medical intervention/therapy required, hospitalisation possible |

The investigator will use the guidelines provided below to assess the relationship of the event to the administration of the vaccine. Both severity of the event and its relationship to the vaccine administration will be documented in the CRF.

Further details for any AE (such as start/stop date and any treatment), will be gathered, regardless of the relationship to the vaccine. We will also document any unsolicited adverse event reported by the volunteer. Serious adverse events (SAE) as defined above will be documented and reported using a serious adverse event reporting form.

### **Follow-up of Adverse Events**

Adverse events likely to be related to the vaccine, whether serious or not, which persist at the end of the trial will be followed up by the investigator until their resolution or stabilisation or until causality is determined to be unrelated to trial interventions.

Moreover, any serious adverse event likely to be related to the vaccine and occurring after trial termination should be reported by the investigator according to the procedure described below.

Outcome of any non-serious adverse event occurring within 30 days post-vaccination (*i.e.* unsolicited adverse event) or any SAE reported during the entire study will be assessed as:

- Recovered/resolved
- Not recovered/not resolved
- Recovering/resolving
- Recovered with sequelae/resolved with sequelae
- Fatal (SAEs only)

Subjects who have moderate or severe on-going adverse events that are not vaccine linked will be referred to an appropriate hospital/health facility at the completion of the study and will be advised to consult a primary care physician if the event is not considered to be related to the study vaccine. A follow-up visit will be arranged to manage the problem and to determine the severity and duration of the event, if it is considered to be related to the study vaccine. If appropriate, specialist review within the King Baudouin hospital of Guediawaye will be arranged.

### **Reporting of Adverse Events**

Every SAE occurring throughout the trial must be reported by telephone, e-mail or fax to the sponsor and DSMB by the investigator as soon as (s)he is alerted of it and within one working

day, even if the investigator considers the AE not related to vaccination. The investigator will then complete a SAE report as soon as possible and within 5 working days or 7 calendar days.

Any relevant information concerning the adverse event that becomes available after the SAE report form has been sent (outcome, precise description of medical history, results of the investigation, copy of hospitalisation report, etc.) will be forwarded to the sponsor in a timely manner, the anonymity of the subjects shall be respected when forwarding this information. Any study-related SUSAR or serious adverse event related to participation in the study must be reported to the ethical review committee (ERC) via email ([contact]) within twenty four (24) hours after the principal investigator (PI) becomes aware of the event. The hard copies of the report must be forwarded to the ERC Secretariat within three (3) working days of the initial notification. Follow-up reports should be submitted as soon as more information becomes available. Periodic safety reports of any study-related expected adverse event or adverse events not related to participation in the study will be forwarded to ERC.

Initial reports of SUSARs should be provided by the Sponsor to the Direction de la Pharmacie et des Laboratoires (DPL) as soon as possible but within seven calendar days of the notification of the SUSARs with follow up reports being provided within a further eight (8) calendar days.

The sponsor pledges to inform the authorities of any trial discontinuation and specify the reason for discontinuation.

The causal relationship between the SAE and the product will first be evaluated by the investigator with the following scale (table 7):

**Table 7: Guidelines for assessing the relationship of vaccine administration to an AE**

|   |                        |                                                                                                                                                                                                                                                |
|---|------------------------|------------------------------------------------------------------------------------------------------------------------------------------------------------------------------------------------------------------------------------------------|
| 0 | No Relationship | No temporal relationship to study product and
Alternate aetiology (clinical state, environmental or other interventions);
and
Does not follow known pattern of response to study product                                |
| 1 | Unlikely        | Unlikely temporal relationship to study product and
Alternate aetiology likely (clinical state, environmental or other interventions) and
Does not follow known typical or plausible pattern of response to study product. |
| 2 | Possible        | Reasonable temporal relationship to study product; or
Event not readily produced by clinical state, environmental or other interventions; or
Similar pattern of response to that seen with other vaccines                  |

|   |                 |                                                                                                                                                                                                                              |
|---|-----------------|------------------------------------------------------------------------------------------------------------------------------------------------------------------------------------------------------------------------------|
| 3 | Probable | Reasonable temporal relationship to study product; and

Event not readily produced by clinical state, environment, or other interventions or

Known pattern of response seen with other vaccines   |
| 4 | Definite | Reasonable temporal relationship to study product; and

Event not readily produced by clinical state, environment, or other interventions; and

Known pattern of response seen with other vaccines |

### **Dissemination and explanation of blood results**

All non-immunological blood results will be given to all participants after screening and at follow-up visits. Immunological results will be explained in general terms, for the group not for individuals, at the end of the study. Those with clinically significant abnormal blood results at screening will be offered appropriate investigations and treatment or referral as necessary.

## **12. DATA HANDLING AND RECORD KEEPING**

### **Data management**

Data management will be conducted in Ucad, and a copy of the anonymized database provided to the sponsor for archiving. The PI will be responsible for receiving, entering, cleaning, querying, analysing and storing all data that accrues from the study. Responsibility for this may be delegated to the study data manager. The data will be entered into the subjects' source documents or offline database. Data will be subsequently transferred to an electronic database for analysis.

If any changes to the study are necessary during the study a formal amendment will be presented to the sponsor prior to submission to the relevant ethical and regulatory agencies for approval unless to eliminate an immediate hazard(s) to study participant without prior ethics approval. Any unforeseen and unavoidable deviations from the protocol will be documented and filed in as a protocol deviation in the Trial Master File, with explanation.

### **Data capture methods**

Data will be captured on to paper source documents for the scheduled clinic visits and home visits, the screening visits, unscheduled clinic visits, and lab and other investigational results.

The paper source documents will be kept securely, but may be taken to the field for direct data entry. Data entry from paper records onto a database will be conducted at UCAD. Immunological data will be transferred to an electronic database for analysis without any volunteer identifier apart from the unique volunteer number.

### **Archiving**

The investigator must keep all trial documents for at least 15 years after the completion or discontinuation of the trial.

### **Protocol deviations**

Any unforeseen and unavoidable deviations from the protocol will be documented and filed in a protocol deviation folder, with explanation.

### **Direct access to Source Data/Documents**

Only the clinical team will have access to the participants' health records and personal information. However, the PI will provide direct access to the source data documents to the ethics committee should this be requested, to the regulatory agency, and to authorised representatives of the sponsor in order to permit trial related monitoring and audits.

## **13. STATISTICS**

### **Sample Size Considerations**

The efficacious malaria vaccine RTS,S/AS02 has been subjected to sporozoite challenge studies in non-immune volunteers (62) as well as field trials in adults in the Gambia (30). In sporozoite challenge, RTS,S/AS02 appears to give 32% sterile protection and 30% partial protection. Efficacy was higher in semi-immune adults in field studies, with 70% during the first 9 weeks of follow up.

Vaccine efficacy of ChAd63/MVA ME-TRAP in sporozoite challenge studies in Oxford was 21% sterile protection with 36% partial protection. We therefore consider it plausible that ChAd63/MVA ME-TRAP might show 50% efficacy in field studies of adults.

Assuming 50% efficacy of vaccination, with an estimated 70% local incidence of malaria by PCR during the follow up period, we expect 93% power to detect, at  $p=0.05$ , an efficacy of 50% and 77% power to detect an efficacy of 40% with 100 volunteers. Allowing for up to 20 volunteers to be lost to follow up, our sample size would be 120.

Below we tabulate the power obtained with differing vaccine efficacies and rates of PCR positivity, assuming  $p=0.05$  and 100 evaluable volunteers completing the study.

It should be noted that the incidence of asymptomatic parasite carriage detected by qPCR was taken to be 70% on the basis of two observations in the literature.

- a) The qPCR technique was used in the Gambia to assess the impact of prospective vaccines on 102 volunteers. The results of follow-up over five months showed that 71% of the volunteers became positive again at some time or other during follow-up (Imoukhuede et al. 2007; see paper attached). We also include a second article by Andrews et al. highlighting the excellent sensitivity of this real-time PCR method.
- b) The second point comes from a meta-analysis of a KEMRI study in Kenya. National Malaria Control Programme data put the estimated prevalence of asymptomatic parasite carriage detected by a rapid diagnostic test at between 26% and 32%. According to Okell et al., there is a linear correlation between the percentage of positive adults in RDTs and the percentage of positive individuals in qualitative real-time PCR. In Kenya, a 30% positive RDT rate corresponded to a 60% positive PCR rate in a cross-sectional study. It is highly likely, therefore, that many more individuals would be positive if, instead of a study over time T, we proposed monitoring volunteers for six months, as the 70% positive rate found by Imoukhuede et al. confirms.

**Table 8:** Power of study with  $n=100$  tabulated by vaccine efficacy and prevalence of PCR positivity

| Prevalence of PCR positivity |     |     |     |     |     |
|------------------------------|-----|-----|-----|-----|-----|
| Vaccine efficacy             |     | 0.8 | 0.7 | 0.6 | 0.5 |
|                              | 50% | 98  | 93  | 83  | 67  |
|                              | 40% | 89  | 77  | 62  | 46  |
|                              | 30% | 67  | 50  | 38  | 27  |

**Safety Review**

No interim safety analysis is planned.

**Immunogenicity or Efficacy Review**

No interim immunogenicity analysis is planned.

***Final Analysis Plan***

Analyses will be performed on subjects with intent to treat (ITT) and according to protocol (ATP).

***Intent-to-treat cohort (ITT)***

The intent-to-treat cohort will include all subjects enrolled in the study, who received at least one dose of the candidate malaria vaccines or comparator and for whom data for the observation in question are available.

***Protocol-defined cohort for analysis of efficacy (ATP)***

The protocol-defined cohort for analysis of efficacy will include all evaluable subjects (i.e., those meeting all eligibility criteria, complying with the procedures defined in the protocol, for whom data concerning efficacy endpoint measures are available.

***Safety data***

All reactogenicity analyses will be on an intention to treat basis, comparing control to malaria vaccine regimen. The frequency of adverse events, changes in ALT, plasma creatinine, haemoglobin, white cell count, platelet values will be described by time and vaccine group.

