## **Study groups**

Subjects will be randomized to receive either ChAd63 ME-TRAP and MVA ME-TRAP or control vaccination with Rabies vaccine. To preserve blinding, Rabies vaccine will be administered in a 0, 2 month schedule. This differs from the standard schedule for rabies vaccination, however, administration of rabies vaccine by alternative schedules may still provide some protective efficacy against rabies. In addition, all participants will be offered a standard schedule of Rabies vaccine after the trial comes to an end.

Simple randomisation into the study groups will be done by an independent statistician and the study clinicians with an allocation ratio of 1:1 to study groups taking into account their area of residence. A randomization code list will be generated by an independent statistician and its use guided by a clear standard operating procedure (SOP). Allocation concealment will be employed by use of opaque sealed envelopes. The volunteers, fieldworkers and laboratory scientists will be blinded to vaccine allocation until the end of the study, but the clinical investigators will not be blinded.

All vaccinations will be administered by the intramuscular route – IM. Randomization into groups will be as follows:

- **Group 1**(60 volunteers): ChAd63 ME-TRAP  $5 \times 10^{10}$  viral particles (vp) followed by MVA ME-TRAP  $2 \times 10^8$  plaque forming units (pfu) 8 weeks later.
- **Group 2**(60 volunteers): control, i.e. Rabies vaccine 1ml followed by Rabies vaccine 1ml 8 weeks later.

Oral antimalarials will be taken by all participants from days 63-65 inclusive. The purpose is to clear any asymptomatic parasitaemia (both asexual blood stage parasites and gametocytes) prior to the commencement of PCR monitoring for new malaria infection from Day 70. A standard 3 day course of Atovaquone/proguanil will be combined with three days of concurrent oral artesunate. Atovaquone/proguanil has been chosen over artemether/lumefantrine to limit the potential for persistence of antimalarial drug from Day 70 when monitoring for new malaria infection commences (lumefantrine has a relatively long elimination half life). Artesunate has been selected because of its antigametocidal activity. The anti- malarial treatment will be directly observed.

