### ***Withdrawal criteria***

Subjects may be withdrawn from the study:

- By withdrawing consent
- On the decision of the investigator
- On the advice of the data safety and monitoring board (DSMB)

The investigator may withdraw the subject for the following reasons:

- Any adverse event which results in the inability to comply with study procedures
- Ineligibility either arising during the study or retrospectively (having been overlooked during screening)
- Significant protocol deviation.
- Loss to follow up (applies to a subject who consistently does not return for protocol study visits, is not reachable by telephone or any other means of communication and/ is not able to be located).

The reason for withdrawal will be recorded in the case report form (CRF).

If a subject is withdrawn for any reason, the reason will be recorded. If withdrawal is the result of a serious AE, the investigator will offer to arrange for appropriate specialist management of the problem and the ethical committee will be informed in a timely manner. The extent of follow up will be determined by a medically qualified investigator, but will be at least for the whole study period. Subjects withdrawn prematurely for any reason will not receive further vaccinations, although they may be requested to come back to the clinic for safety evaluation.

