### ***Indications for delayed vaccination.***

The following adverse events constitute contraindications to administration of vaccine at that point in time; if any one of these adverse events occurs at the time scheduled for vaccination, the subject may be vaccinated at a later date, or withdrawn at the discretion of the investigator. The subject must be followed until resolution or stabilization of the adverse event or until causality is determined to be unrelated to trial interventions, as with any adverse event.

- Acute disease at the time of vaccination. (Acute disease is defined as the presence of moderate or severe illness with or without fever). Vaccines can be administered to persons with a minor illness such as diarrhoea, mild upper respiratory infection with or without low-grade febrile illness, i.e., temperature of  $<37.5^{\circ}\text{C}/99.5^{\circ}\text{F}$ ).
- Temperature of  $\geq 37.5^{\circ}\text{C}$  ( $99.5^{\circ}\text{F}$ ) at the time of vaccination.

**NB:** Anaphylactic reaction following administration of study vaccine constitutes an absolute contraindication to further administration of vaccine, and the subject must be withdrawn and followed until resolution of the event

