#### **D 57 (Field worker visit)**

Each volunteer will be visited at home on day 57 by a field worker for assessment and recording of any solicited and unsolicited AEs in the diary card. If necessary the volunteer will continue to be seen regularly until the symptom(s) have resolved or stabilised. Venepuncture for gene expression studies will be done on the 30 Group A volunteers, as close to 24 hours post-vaccination as practicable.

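### The reactogenicity set follows allocation and available data, not receipt of the dose, so unboosted volunteers can remain in post-dose-2 general adverse event and laboratory tables

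*Protocol*

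**What the plan says.** Protocol section 13, Safety data, sets the basis for reactions: "All reactogenicity analyses will be on an intention to treat basis, comparing control to malaria vaccine regimen". The next sentence covers adverse event frequency, ALT, creatinine and blood counts; it ends "platelet values will be described by time and vaccine group" and names no exposure condition.

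The intention-to-treat cohort in the same section consists of enrolled subjects "who received at least one dose of the candidate malaria vaccines or comparator and for whom data for the observation in question are available". The only other set is introduced with "The protocol-defined cohort for analysis of efficacy will include all evaluable subjects", so it serves efficacy. The Protocol defines no safety set by product received and no set of second-dose recipients.

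Section 9 (Study groups) makes the two active injections different products: ChAd63 ME-TRAP first, MVA ME-TRAP eight weeks later, in 60 volunteers. The 60 controls receive rabies vaccine twice.

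Section 9 also foresees volunteers who miss the second injection. Under Indications for delayed vaccination, "the subject may be vaccinated at a later date, or withdrawn at the discretion of the investigator". Under Withdrawal criteria, "Subjects withdrawn prematurely for any reason will not receive further vaccinations, although they may be requested to come back to the clinic for safety evaluation".

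**The concern.** Keeping volunteers in the arm to which they were randomised protects an efficacy comparison. For reactions, the question is what the injected products do. Leaving in people who did not receive an injection, or booking a reaction under a product that was not given, tends to make the arms look alike. For safety that is the unsafe direction.

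The omission may also be selective. Both the delay and the withdrawal rules make illness or an adverse event a route to missing the second dose, so the unboosted may include those who reacted to the first.

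The Protocol settles this point. Safety data says that all reactogenicity analyses are by intention to treat, so a statistical analysis plan that grouped reactions by product received would have to depart from that sentence.

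**Working it through.** The Protocol gives no planned reaction rate and no number expected to miss the second dose, so there is no plan figure to reproduce. The check has two parts.

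**1. Who can enter a post-dose-2 table without the second dose?**

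- *Local reactions.* Table 1 lists them as injection-site events. With no second injection there is nothing to observe, and the availability condition removes the volunteer.
- *The D57 home visit.* The visit text reads "Each volunteer will be visited at home on day 57 by a field worker for assessment and recording of any solicited and unsolicited AEs", but the Follow-up section ties home visits to the day after each vaccination. An unboosted volunteer would probably have no such visit, so I place no weight on D57.
- *D63 and later.* Adverse events are recorded at D63, at the PCR visits from D70 to D119 and at D161. ALT, creatinine and full blood count are repeated at D63 and D161. Section 10 (below Table 5) has general as well as local side effects asked about at each visit. Withdrawn volunteers may be called back for safety, and a volunteer with a contraindication at the scheduled vaccination is followed until the event resolves or stabilises, or is judged unrelated. Fever, malaise, headache, myalgia and laboratory values can therefore be available after D56 for someone who never had the second dose. The cohort definition keeps that person in.

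**2. How large is the effect?**

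Inputs: 60 per arm (Study groups). Assumed: true event rate r among second-dose recipients; k volunteers unboosted but observed; no event among those k.

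Tabulated rate = r × (60 − k)/60.

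| True rate r (assumed) | k = 1 | k = 2 | k = 3 |
|---|---|---|---|
| 20% | 19.7% | 19.3% | 19.0% |
| 40% | 39.3% | 38.7% | 38.0% |
| 60% | 59.0% | 58.0% | 57.0% |
| 80% | 78.7% | 77.3% | 76.0% |

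For example, 0.60 × 57/60 = 0.57. With 60 − k as the denominator, the dilution disappears. If the unboosted have some background events, the dilution is smaller than shown.

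*Effect on the difference.* Take assumed rates of 60% active and 20% control, a true difference of 40 points.
- k = 3 in both arms: 57% − 19% = 38 points.
- k = 3 in the active arm only: 57% − 20% = 37 points.
- k = 3 in the control arm only: 60% − 19% = 41 points.

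The difference narrows when the missed doses are balanced or fall mainly in the active arm. It widens slightly if they fall only among controls.

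*Wrong product given.* If m of 60 controls receive the active vaccine and are analysed as allocated, the control rate becomes (pc × (60 − m) + pv × m)/60. At assumed rates pv = 80% and pc = 20%:
- m = 1: (0.20 × 59 + 0.80 × 1)/60 = 21%.
- m = 3: (0.20 × 57 + 0.80 × 3)/60 = 23%.

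**The case against.** The strongest reply is that the Protocol's rule is coherent. The secondary objective concerns the safety of a prime-boost strategy, and Safety data compares regimen with control. No MVA-specific rate or denominator is stated that could be biased, and description by time already separates visits after the first dose from visits after the second. The availability condition removes the obvious cases, postponed volunteers may still be boosted, and per-dose denominators are often left to the analysis plan.

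Much of this stands. The regimen comparison is legitimate and should be kept, and the availability condition probably does settle local reactions. But tabulating by time separates visits, not exposure. Data can exist without the dose, and the word all in Safety data leaves no place for an analysis by product received.

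A further objection also stands: second-dose recipients are a selected group who went on after the first dose. A table restricted to them says nothing about those who stopped, so it needs the count of unboosted volunteers beside it.

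A reader might infer three stronger things that the Protocol does not support:
- That every unboosted volunteer stays in the MVA denominator. The cohort has two conditions, and the second removes many of them.
- That dilution could reach 10 of 60, taking half of the sample-size allowance of 20 lost to follow-up. Withdrawal criteria describes such volunteers as not returning and not reachable. They are not observed, so they contribute no dilution.
- That mis-dosing is expected. None is reported, and the cohort definition does not itself say as randomised; that part rests on the usual meaning of intention to treat.

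**Conclusion.** The point holds in a limited form. The Protocol fixes intention to treat for all reactogenicity analyses and conditions on data rather than exposure. General adverse event and laboratory tables after D56 can therefore include volunteers who did not receive the second dose, and a wrongly dosed volunteer would be counted under the allocated vaccine.

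The size is probably small: 1 to 3 percentage points on an assumed 60% rate with 1 to 3 unboosted but observed volunteers. A single wrongly dosed control moves the control rate by about 1 point even at assumed rates of 80% and 20%. The bias is toward no difference, provided missed second doses are balanced or mainly in the active arm. The rates, the number unboosted and the number mis-dosed are all assumptions. Efficacy is unaffected. Label: cheap improvement.

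**What to change.** Replace the first sentence of Safety data in section 13 with wording such as: *Reactogenicity and adverse events will be tabulated after each dose among volunteers who received that dose, grouped by the product actually injected (ChAd63 ME-TRAP, MVA ME-TRAP, rabies vaccine dose 1, rabies vaccine dose 2). The as-randomised comparison of the whole regimen with control will be presented alongside. The number of volunteers not given the second dose, with reasons, will be reported by arm.* Apply the same denominators to laboratory values after the second dose.

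The cost is one short edit and one extra set of tables from data already collected. The selection among second-dose recipients remains; reporting the unboosted and their reasons makes it visible. The efficacy analysis stays as randomised.
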